### 6.2 Study procedures

Phase 1a: dPET/CT + static PET/CT (n=5)

Phase 1b: static PET (n=25, total=30)

A schedule for one patient is as follows:

First scan  $^{68}\text{Ga}$ -PSMA PET/CT scan as planned (standard clinical care).

Second scan~4 weeks later:  $^{68}\text{Ga}$ -PSMA PET/CT scan (additional for research purposes).

The  $^{68}\text{Ga}$ -PSMA PET/CT scan will be performed according to standard protocol. Patients will receive a venous catheter through which  $\pm 100$  MBq of  $^{68}\text{Ga}$ -PSMA is administered (maximum 10 mL). The catheter is then flushed with 10 ml of saline and removed. After 45 minutes a PET scan is performed directly followed by a low-dose CT scan. When the scans are finished, the patient can leave the hospital. The total procedure (including injection, resting, and scanning) lasts 1.5 hours.

Five patients will undergo a dPET/CT scan as well as a static PET/CT scan. To perform a dPET/CT scan, first a CT scan of the pelvis is made to ensure the location of the prostate. Thereafter, the patient will be injected with  $^{68}\text{Ga}$ -PSMA while lying in the PET/CT scanner. Accordingly, the patient is continuously imaged for 40 minutes. After the scan, the patient is requested to void to better visualize the prostate. Then the standard static PET/CT scan is performed. This study does not interfere with standard clinical care. Both treatment and diagnostic procedures will not be altered or postponed for this study.

### 6.3 Withdrawal of individual subjects

Subjects can leave the study at any time for any reason if they wish to do so without any consequences. The investigator can decide to withdraw a subject from the study for urgent medical reasons. The investigator can decide to withdraw a subject from the study if on the first scan there is no PSMA expression visible. This can occur in 3% of the population. In this case, a second scan would not be useful as well.

### 6.4 Replacement of individual subjects after withdrawal

In case a subject does withdraw from the study or has no PSMA expression on the first PET scan a replacement is sought.

## **6.5 Follow-up of subjects withdrawn from treatment**

Not applicable.

## **6.6 Premature termination of the study**

Reasons for premature termination of the study are:

- Occurrence of any serious adverse events that can in anyway be related to the study.

## **7. STATISTICAL ANALYSIS**

### **7.1 Primary study parameter(s)**

All the data will be collected and quantitatively analysed within the NKI-AvL. The number and location of lesions are determined by a nuclear medicine physician. The absolute uptake in Bq/mL of the voxels will be determined using standard software (Osirix MD viewer). A paired t-test is used to compare uptake values of  $^{68}\text{Ga}$ -PSMA of the first and the second scan.

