### 3.1 PSMA expression over time

The aim is to obtain preliminary data on variability in PSMA receptor expression by comparing prostate uptake on standard clinical  $^{68}\text{Ga}$ -PSMA PET/CT with additional  $^{68}\text{Ga}$ -PSMA PSMA PET/CT in a 4 week interval.

Primary prostate cancer patients will be included using routine MRI examinations. Based on protocol, a  $^{68}\text{Ga}$ -PSMA PET/CT scan will be advised on high risk prostate cancer patients (cT3, Gleason score >7, PSA >20 ng/mL). These patients will be asked to participate in the study. If they agree to participate, the patients will undergo another  $^{68}\text{Ga}$ -PSMA PET/CT scan within 4 weeks after the routine diagnostic scan. The protocol for the second scan is equal to the standard diagnostic  $^{68}\text{Ga}$ -PSMA PET/CT scan. The PET scan will be acquired at approximately 45 minutes after administration of ~100MBq  $^{68}\text{Ga}$ -PSMA.

In the 5 patients, a dynamic PET/CT-scan (dPET/CT) is acquired up to 40 minutes after administration of the radiopharmaceutical. The dPET/CT scan is performed at one bed position with the prostate in the central field-of-view (FOV). The low-dose CT scan of the same region is made before tracer injection, for attenuation correction and anatomic localization. dPET/CT imaging is started immediately after intravenous injection of 100 MBq  $^{68}\text{Ga}$ -PSMA.

The static PET/CT acquisition is performed directly after the dynamic series. Between the dynamic and static acquisition, the patient is requested to void.

**Table 1.** Division of subgroups in the clinical phase.

| Phase                   | Subgroup   | Administration for PET (MBq) |
|-------------------------|------------|------------------------------|
| 1a – dynamic and static | I. n = 5   | 100                          |
| 1b – static             | II. n = 25 | 100                          |

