## 6. METHODS

### 6.1 Study parameters/endpoints

The main study endpoint is to evaluate the PSMA expression variation at 4 week intervals, in terms of uptake difference in prostate and surrounding tissue). The secondary endpoint is to determine the optimal time between  $^{68}\text{Ga}$ -PSMA injection and prostate surgery for future image-guided surgery using Cherenkov Light Imaging. Randomisation, blinding and treatment allocation

No randomization will take place. Scans will be anonymized. Each patient will be assigned a consecutive number. The first and the second scan will be assigned the letter 'A' or 'B', respectively. Only the researchers will be able to see the key, which allocates study numbers to patients. A nuclear medicine physician will assess the anonymized  $^{68}\text{Ga}$ -PSMA PET/CT scans for differences in uptake. This physician is blinded to the order and correspondence between scans.

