### **7.2 Secondary study parameter(s)**

The  $\text{Bq/mL}_{\text{peak}}$ , derived from the PET scan, and the size, derived from the low-dose CT scan, are determined of each lesion. These values will be compared between both scans.

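### Uptake is compared between scans in absolute Bq/mL, so scan-to-scan differences in injected activity and timing are mixed into the measured change in PSMA expression

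*Protocol*

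**What the plan says.** Protocol section 7.1 defines the primary measurement: "The absolute uptake in Bq/mL of the voxels will be determined using standard software (Osirix MD viewer"). It then names the test: "A paired t-test is used to compare uptake values of" the tracer on the first and second scan.

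Section 7.2 takes a peak value in Bq/mL per lesion, "derived from the PET scan, and the size, derived from the low-dose CT scan, are determined of each lesion", and adds: "These values will be compared between both scans".

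Section 6.1 gives the meaning of the endpoint. It is variation in PSMA expression over four weeks, "in terms of uptake difference in prostate and surrounding tissue".

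Activity and timing are described in section 3.1: "The PET scan will be acquired at approximately 45 minutes after administration of ~100MBq" of the tracer. Section 6.2 repeats the timing: "After 45 minutes a PET scan is performed directly followed by a low-dose CT scan". Neither section gives a tolerance for activity or start time. The control on comparability is in section 3.1: "The protocol for the second scan is equal to the standard diagnostic" scan.

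The protocol nowhere mentions division by injected activity, SUV, decay correction to injection time, a reference-tissue ratio, or recording of the actual activity and start time at each visit.

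**The concern.** The quantity of interest is PSMA expression, but the analysed quantity is activity concentration. For a given patient, expression and time after injection, activity concentration rises and falls in proportion to the activity injected. It also depends on when the scan starts, through physical decay (unless corrected) and through the time course of uptake. The protocol accepts that time course, since its secondary objective is to find the best scan time.

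Differences in delivered activity or start time between a patient's two scans are therefore mixed into the change that is read as a change in expression. Random differences add variance. That matters here because the primary objective is to describe variability. A systematic difference between first and second scans would also bias the mean paired difference. The Summary and section 1 intend the result to support inclusion and dose determination for image-guided surgery from the clinical scan, so a technical contribution should not be read as biology.

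The unit is stated in the protocol. This is a choice made, not a detail left to a statistical analysis plan.

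**Working it through.** **Inputs from section 4.4.** 30 pairs, 80% power, equivalence margin ±30%, expected difference at most 10%, CV 0.6 to 0.7, within-subject correlation ρ 0.8 to 0.85. No alpha is stated; one-sided 5% is assumed.

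**Step 1: reproduce the planned size.** SD of the paired difference, as a fraction of the mean: SD = CV × √(2(1 − ρ)).
- CV 0.6, ρ 0.85: 0.6 × √0.30 = 0.329
- CV 0.7, ρ 0.8: 0.7 × √0.40 = 0.443

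n = [SD × (1.645 + 0.842) / (0.30 − 0.10)]² gives 16.7 (17) and 30.3 (31). The stated 30 is reproduced, to within rounding, at the conservative corner. Power at n=30 from two one-sided t-tests is 95% and 78% respectively.

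**Step 2: effect of the unit on one pair.** Bq/mL is proportional to injected activity at equal expression and time.
- 110 / 100 = 1.10 reads as +10%. This equals the expected difference and is 10/30 = one third of the margin.
- 130 / 100 = 1.30 reads as +30%, the whole margin.

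These activities are illustrations; the documents report no actual values.

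**Step 3: random activity variation.** Assume independent variation with SD c per scan that is not already inside the stated CV and ρ. Then SD′ = √(SD² + 2c²).

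| c | SD′ (CV 0.6, ρ 0.85) | Power, n=30 | SD′ (CV 0.7, ρ 0.8) | Power, n=30 |
|---|---|---|---|---|
| 0 | 0.329 | 95% | 0.443 | 78% |
| 5% | 0.336 | 94% | 0.448 | 77% |
| 10% | 0.358 | 91% | 0.465 | 74% |
| 20% | 0.434 | 79% | 0.525 | 64% |

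The true difference is 10% throughout. Letting the noise scale with each patient's own uptake, so that 2c² becomes 2c²(1 + CV²), gives somewhat lower power: 93% and 77% at 5%, 90% and 73% at 10%, and 74% and 59% at 20%.

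**Step 4: a hypothetical systematic shift.** If one visit read 10% differently for technical reasons, in the same direction as a true 10% difference, the total would be 20%. Power would be 49% (CV 0.6, ρ 0.85) or 33% (CV 0.7, ρ 0.8). With no true change, the same 10% shift alone leaves equivalence power at 95% or 78%. In that case the paired t-test of section 7.1, at two-sided 5%, would report a difference in 36% or 22% of trials.

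**Step 5: timing.** This step applies only if images are not decay-corrected to injection. With an assumed Ga-68 half-life of 67.7 minutes, a 10-minute later start gives 1 − 2^(−10/67.7) = 0.097, a fall of about 10%. Half-lives of 65 to 70 minutes give 10.1% to 9.4%.

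**The case against.** The strongest reply is that the comparison is within patient and under one nominal protocol. Section 3.1 makes the second scan equal to the standard one, and section 5.6 allows no dosage modification. This stands against any claim of bias: nothing in the documents suggests that one visit has systematically different activity or timing. It does not answer the variance point, because an equal nominal activity is not an equal delivered activity.

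Second, section 4.4 bounds the difference between measurements, not between true expression levels. Technical variation may already sit inside that 10%, the CV and the correlation. This also stands. The source of those figures is not given, so it is unclear whether they refer to Bq/mL or to a normalised measure. The losses in steps 3 and 4 are conditional on that.

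Third, images may be decay-corrected to injection by default. That would remove the physical-decay effect in step 5, but not the effect of injected activity or of the uptake time course.

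Fourth, section 6.1 refers to prostate and surrounding tissue. A difference between two Bq/mL values still scales with injected activity; only a ratio would cancel it.

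Fifth, absolute activity has its own use for Cerenkov imaging. That is a reason to report it, not to use it as the measure of stable expression.

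A reader might infer that the study measures injection and timing differences instead of expression, or that a 10% technical shift exhausts the equivalence allowance. The documents support neither. Technical differences are one component of the measured change, and 10% is one third of the 30% margin.

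**Conclusion.** The point holds as a should-fix. Sections 7.1 and 7.2 compare a quantity that depends on delivered activity and scan time and read it as PSMA expression, while both are specified only nominally. The proportionality to activity needs no assumption about spread. The cost in power does: it is about 1 percentage point at an activity SD of 5% per scan, about 4 points at 10%, and 14 to 15 points at 20%, if that variation is not already in the planning figures. The fall to 33-49% needs a systematic 10% shift on top of the planned 10%, for which the documents give no ground, so it is a sensitivity figure and not an expectation.

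The sample size is not wrong on this account. A reader might also conclude that the results could not be rescued. That does not follow: if actual activities and times are recorded, values can be converted afterwards. The protocol does not say that they will be.

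**What to change.** - In sections 7.1 and 7.2, define the compared value, both primary and peak, as activity concentration decay-corrected to injection time and divided by net injected activity (residual subtracted). Adding body weight makes this an SUV; weight scaling matters little within a patient over about four weeks.
- Keep raw Bq/mL as a descriptive output for the Cerenkov work.
- Record and report the actual injected activity and the injection-to-scan time for both scans of each pair. Normalisation does not remove the dependence of uptake itself on time, so readers need to see how closely the times matched.
- State in section 4.4 which measure the CV and correlation refer to.

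The cost is an edit to each of these sections and a little more data recording and analysis. No additional scan or patient is needed.

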Ga-PSMA is an emerging imaging agent that already has been widely proven as a highly effective agent for restaging PCa cells, but also holds enormous potential for initial staging and image guided surgery. During surgery, Ga-PSMA can be probably be used of assessment of the resection margins based on Cerenkov Light emission. This is part of study granted by KWF (grant number 15175). The interval between initial staging and its application in surgical setting, however, ranges from 4 to 6 weeks. Since little is known about the PSMA expression over time without intervention, a study on this is required to verify this. If PSMA expression is equal between both scans, the inclusion and dose determination can be based on the clinical PET/CT scan. In order to validate this, two PET scans will be performed in a test-retest setting in primary prostate patients. Dynamic imaging will be performed in order to get insight into the most ideal scan time. Subsequently this will be used also to establish the ideal timing of surgery after injection.

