### 4.4 Sample size calculation

Paired measurements of 30 patients will provide 80% to show the equivalence of the two tests (4 weeks before surgery and 1 day before surgery) assuming that accepted boundary of equivalence is symmetric and equals 30%. A variation more than 30% is considered clinically relevant, according to PERCIST criteria. We expect that the second measurement will be different from the first measurement by no more than 10%. Coefficient of variation is assumed to be between 0.6 and 0.7 and within-subject correlation is assumed to be 0.8-0.85.

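### The study is sized to show equivalence of the two scans within 30%, but the primary analysis is a paired t-test of no difference that never uses that boundary

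*Protocol*

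**What the plan says.** **Sample size (Protocol 4.4).** The claim is "Paired measurements of 30 patients will provide 80% to show the equivalence of the two tests", where the "accepted boundary of equivalence is symmetric and equals 30" percent. The margin has a clinical reason: "A variation more than 30% is considered clinically relevant". On the true shift, the plan says: "We expect that the second measurement will be different from the first measurement by no more than 10" percent. The other inputs are a coefficient of variation of 0.6 to 0.7 and a within-subject correlation of 0.8 to 0.85. No alpha is given, and the word power is missing after the 80%.

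**Purpose (Protocol, Summary and section 1).** The intended use depends on the scans agreeing: "If PSMA expression is equal between both scans, the inclusion and dose determination can be based on the clinical PET/CT scan".

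**Analysis (Protocol 7.1).** Uptake is measured in Bq/mL, and "A paired t-test is used to compare uptake values of" the tracer on the first and second scan. This is the only primary analysis named. Section 7.2 says only that lesion peak uptake and size will be compared between scans. The 30% boundary appears nowhere in section 7.

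**The concern.** The two sections test opposite hypotheses. An equivalence test takes as its null a shift of at least 30% and must reject that to succeed. The paired t-test takes as its null a shift of zero, so the result the study hopes for is a failure to reject.

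Three things follow:

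- A non-significant result leaves equivalence unproven.
- A significant result may reflect a shift well inside the boundary that the protocol itself accepts.
- The 80% in 4.4 does not describe the analysis in 7.1.

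The statement in section 1 about relying on the clinical scan would then rest on a test that cannot support it. A shift that the protocol regards as unimportant could be reported as a change in expression.

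**Working it through.** **Inputs, all from Protocol 4.4.** n = 30 pairs; margin m = 0.30; true shift δ = 0.10; CV 0.6 to 0.7; correlation ρ 0.80 to 0.85. Alpha is not stated, so one-sided 5% is assumed first and 2.5% is shown for comparison. Differences are expressed as a fraction of the mean and taken as normal.

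**Step 1: SD of the paired difference.** SD = CV × √(2(1 − ρ)), and SE = SD/√30. For CV 0.7 and ρ 0.80: 0.7 × √0.40 = 0.443, and SE = 0.443/5.477 = 0.0808.

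**Step 2: reproduce the plan's figure.** For two one-sided tests, the normal approximation is power = Φ((m − δ)/SE − 1.645). With CV 0.7 and ρ 0.80: 0.20/0.0808 − 1.645 = 0.83, so power is 79.7%. The matching sample size is (0.443 × (1.645 + 0.842)/0.20)² = 30.3, or 31 pairs. The stated 30 pairs and 80% are thus an equivalence calculation at the pessimistic end of the inputs. At one-sided 2.5%, CV 0.7 with ρ 0.85 also comes close (81.5%, n = 29), so the text does not reveal which alpha was used.

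**Step 3: compare the two tests.** The equivalence test succeeds if the 90% confidence interval (estimate ± 1.699 SE, 29 df) lies within ±0.30. The t-test is significant at two-sided 5% if the absolute estimate exceeds 2.045 SE. Power is computed with the t distribution.

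| CV | ρ | SD | Equivalence shown, true 10% | t-test significant, true 10% | Both at once, true 10% | t-test non-significant, true 30% |
|---|---|---|---|---|---|---|
| 0.6 | 0.85 | 0.329 | 94.6% | 36% | 31% | 0.2% |
| 0.6 | 0.80 | 0.379 | 88.0% | 29% | 17% | 1.3% |
| 0.7 | 0.85 | 0.383 | 87.4% | 28% | 16% | 1.5% |
| 0.7 | 0.80 | 0.443 | 77.9% | 22% | 6% | 5.2% |

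The column headed both at once counts studies in which the data meet the 30% equivalence criterion and the planned test still reports a difference.

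**Step 4: sensitivity.**

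- *Alpha.* At one-sided 2.5%, normal-approximation equivalence power runs from 69.7% to 91.5% over the same inputs.
- *Noise.* If the SD of the difference were 0.8, an assumption well outside the plan's range, the t-test would be non-significant at a true 30% shift in 49% of studies.
- *Scale.* On the log ratio with limits 0.70 to 1.30, a true ratio of 1.1 and one-sided 5%, power for CV 0.7 and ρ 0.80 is 72% if the correlation applies to log values and 78% if it applies to raw values.

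**The case against.** **The aim is modest.** Section 2 asks only for preliminary data on variability, the sentence on later use is conditional, and section 6.2 says care is not altered. That limits the consequences. It does not remove the contradiction, because 4.4 still claims power to show equivalence.

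**The analysis plan may settle it.** An unseen plan could add detail, and a paired t statistic can underlie two one-sided tests. But 7.1 names a specific test and mentions no boundary, interval or one-sided testing. As written, it conflicts with 4.4.

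**The t-test would catch a relevant change.** This is right under the planning inputs. A reader might infer that the planned test is likely to pass off a 30% change as equality. The figures do not support that: it would do so in at most 5.2% of studies, about the 5% error that an equivalence test allows. It is true in principle that imprecise data favour a finding of no difference, but this matters only if variability exceeds the stated range. Nor is a non-significant result at a true 20% shift an error, since 20% lies inside the boundary.

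**The Bq/mL scale.** A reader might also infer that the raw scale is wrong because a CV of 0.6 to 0.7 implies skewed uptake. The documents do not establish this. That CV describes spread between patients, whereas the paired test depends on within-patient differences. A 30% margin can be expressed as a fraction of the mean, as the reproduction of the 80% shows. Normalisation or transformation is not ruled out either. All that stands is that margin and analysis must use the same scale.

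**Conclusion.** The contradiction between 4.4 and 7.1 is real and lies within the protocol. The sample size is sound for an equivalence test: 30 pairs give 78-95% power at a 10% shift and one-sided 5%. The planned t-test answers another question. At that same acceptable shift it would report a difference in 22-36% of studies, and in 6-31% it would do so although the data meet the equivalence criterion. The likely harm is a tolerable shift presented as a change, rather than false reassurance.

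These figures rest on normal paired differences, the plan's CV and correlation ranges, and an assumed alpha. They concern the mean shift only. With the same SDs and a 10% mean shift, 38-51% of individual patients would still differ by more than 30%, so equivalence of the mean would not by itself show that each patient's two scans agree.

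**What to change.** 1. **Section 7.1:** replace the paired t-test as primary analysis with a paired equivalence test (two one-sided tests) against the stated boundary. Declare equivalence only if the 90% confidence interval of the mean relative difference lies within ±30%. Say that a non-significant test of difference is not evidence of equality.
2. **Section 4.4:** state alpha. One-sided 5% approximately reproduces the 80%, with 78% in the worst case by the t distribution. Name the 80% as power.
3. **Both sections:** use one scale for margin and analysis. A log-ratio analysis is an option, not a requirement. If it is chosen, restate the limits, because 0.70 to 1.30 is not symmetric on the log scale (−0.357 to +0.262). Restate the power too (worst case about 72-78%).

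The cost is a change of wording in two sections. With one-sided 5% on the relative-difference scale, no extra patients are needed.

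### The study is sized to show equivalence within ±30%, but the primary test named is a paired t-test that does not use that boundary and cannot by itself support a conclusion of equal uptake

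*Protocol*

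**What the plan says.** Section 4.4 states the aim of the sample size as equivalence: "Paired measurements of 30 patients will provide 80% to show the equivalence of the two tests". The limit is symmetric: "accepted boundary of equivalence is symmetric and equals 30" percent. Its basis is clinical relevance: "A variation more than 30% is considered clinically relevant, according to PERCIST criteria". The assumed truth lies well inside it: "We expect that the second measurement will be different from the first measurement by no more than 10" percent. The spread is also given: "Coefficient of variation is assumed to be between 0.6 and 0.7", with a within-subject correlation of 0.8 to 0.85. No alpha is stated.

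Section 7.1 gives the only primary test: "A paired t-test is used to compare uptake values of" the tracer between first and second scan. It mentions no boundary, confidence interval or one-sided tests. The 30% limit appears nowhere outside section 4.4.

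The Introduction (section 1) attaches a decision to the result: "If PSMA expression is equal between both scans, the inclusion and dose determination can be based on the clinical PET/CT scan". The Summary says the same in its rationale.

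**The concern.** A paired t-test in its ordinary form takes zero difference as its null hypothesis. A significant result says that the mean change is not zero, not that it exceeds 30%. A non-significant result says that zero has not been excluded, not that the change is small. Section 4.4 asks whether the mean change lies within ±30%, and neither outcome of the test in section 7.1 answers that.

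Two things are at stake. First, the 80% in section 4.4 describes an analysis that section 7.1 does not plan. Second, the decision about relying on the clinical scan depends on expression being equal, and the protocol gives no rule by which the named test could establish this. A shift that section 4.4 regards as acceptable could also be reported as a significant difference.

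**Working it through.** **Inputs (section 4.4).** n = 30 pairs; boundary ±0.30; true shift 0.10; CV 0.6-0.7; correlation ρ 0.80-0.85. Alpha is not given. I assume one-sided 5% for each of the two one-sided tests (90% interval) and show 2.5% (95% interval) beside it. The t-test is taken as two-sided 5%. Differences are expressed as a fraction of mean uptake.

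**Step 1: SD of the paired difference.** SD = CV × √(2(1 − ρ)).
- Best corner: 0.6 × √0.30 = 0.329.
- Worst corner: 0.7 × √0.40 = 0.443.

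**Step 2: reproduce the stated 80%.** At the worst corner the standard error is 0.443/√30 = 0.0808. By normal approximation, equivalence power at one-sided 5% is Φ((0.30 − 0.10)/0.0808 − 1.645) = Φ(0.83) = 79.7%. The matching sample size is (1.645 + 0.842)² × 0.443² / 0.20² = 30.3. The stated 30 patients and 80% are therefore recognisable as an equivalence calculation. With t quantiles, integrating over the sample SD, power is 77.9% and 32 pairs are needed for 80%.

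**Step 3: compare with the planned test.** The t-test columns use the noncentral t distribution with n = 30.

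| CV, ρ | SD | Equivalence power at 10% shift, one-sided 5% | Same, one-sided 2.5% | t-test significant at 10% shift | t-test non-significant at 30% shift |
|---|---|---|---|---|---|
| 0.6, 0.85 | 0.329 | 94.6% | 89.6% | 36.4% | 0.2% |
| 0.6, 0.80 | 0.379 | 88.0% | 79.7% | 28.7% | 1.3% |
| 0.7, 0.85 | 0.383 | 87.4% | 78.8% | 28.2% | 1.5% |
| 0.7, 0.80 | 0.443 | 77.9% | 66.5% | 22.3% | 5.2% |

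At neither the expected shift nor the boundary does the t-test have 80% power: it has 22-36% at a 10% shift and 95-99.8% at 30%. The alpha cannot be inferred from the 80% either. One-sided 5% gives about 80% at the worst corner, and one-sided 2.5% gives about 80% at both middle rows.

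**Step 4: how often the two analyses conflict.** By simulation at a true 10% shift, the t-test is significant while the equivalence test succeeds in 31% of studies at CV 0.6, ρ 0.85, and in 6% at CV 0.7, ρ 0.80.

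**Step 5: the scale matters.** The figures above are for the mean paired difference divided by mean uptake.
- On the log scale, with limits ±ln 1.3 and a true shift of ln 1.1, power with 30 pairs at one-sided 5% is 72-90%.
- For the average of per-patient percentage changes, assuming lognormal uptake (the protocol gives no distribution), a 10% shift in means becomes an average change of about 15-18%, and power falls to about 46-78%.

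**The case against.** A statistical analysis plan may exist, two one-sided tests are themselves paired t-tests, and section 7.1 states neither a null hypothesis nor a decision rule, so the equivalence rule might be set out elsewhere. The study also describes its aim as preliminary data. These points soften the finding but do not remove it. The protocol does not leave the test open: it names one without the boundary, while section 4.4 makes a formal equivalence claim.

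A reader might infer that the sponsor intends to read p > 0.05 as equality. No section says so, and it should not be attributed to the protocol. All that can be said is that the named test, as written, offers no valid route to that conclusion.

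A reader might also infer a large risk of wrongly declaring the scans equal. Section 4.4's inputs do not support this. At a true 30% mean shift the t-test misses in 0.2-5% of studies, about what an equivalence test at one-sided 5% would allow, because the 95% interval has a half-width of only about 12-17%. Much larger miss rates require a lower correlation than the protocol assumes, or far fewer pairs, and sections 4.1 and 6.4 provide for replacing patients. Nor is a non-significant result at a 20% shift an error, since 20% lies inside the boundary. The main error on the planned inputs runs the other way, towards reporting a difference that section 4.4 accepts.

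**Conclusion.** The mismatch between sections 4.4 and 7.1 is real and lies in the protocol's own text. The stated 80% reproduces, approximately, for two one-sided tests against ±30% and not for the paired t-test as an ordinary test of zero difference. The main consequence on the planned inputs is that 22-36% of studies would report a significant difference at the expected 10% shift. A non-significant result would not demonstrate equality, although with 30 pairs and the planned SD it would seldom conceal a 30% mean shift.

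This rests on section 4.4's CV and correlation ranges, approximately normal paired differences, a two-sided 5% t-test and the relative scale described above. It concerns the mean change only; neither test shows that individual patients stay within 30%.

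**What to change.** In section 7.1, make two one-sided paired tests against ±30% the primary analysis: equivalence is concluded only if the confidence interval for the mean change lies wholly within the boundary. Fix the scale, either as the mean paired difference divided by mean first-scan uptake, which matches the sizing, or as the log ratio with stated limits that correspond to the 30% boundary. Do not use the average of per-patient percentage changes, which the sizing does not cover. Keep the paired t-test as a descriptive result, and say that non-significance is not taken as equality.

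In section 4.4, state the alpha and tie the power to this test. Over the stated CV and correlation ranges it is about 78-95% at one-sided 5% (90% interval) or about 66-90% at one-sided 2.5% (95% interval). Recompute it if the log scale is chosen.

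The cost is a rewording of two sections and a short calculation, with the same patients and scans. The downside is that a non-significant t-test can no longer be presented as stability, and that the exact power is slightly below 80% at the pessimistic corner even at one-sided 5% (77.9%).
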